### Plans to promote participant retention and complete follow-up {18b}

To promote retention and complete follow-up data collection, the timing and methods of follow-up appointments will be discussed with participants at baseline and an appointment card and customised fridge magnet will be sent to participants. A £40 thank-you voucher is given to participating caregivers at completion of the endpoint questionnaire; school staff are sent a £10 voucher to acknowledge their efforts in questionnaire completion. Regular trial newsletters will be sent to participating families, thanking them for their commitment to the trial.

### Data management {19}

Data management procedures can be found in a Standard Operating Procedure, available on request from the corresponding author. All data in the trial will be anonymised. A central master file of personal data will be held securely in the University of Manchester research office, to be used for operational purposes, and this will contain the key linking anonymised participant IDs to personal details. Trial data will be entered by research staff into the online Elsevier MACRO EDC system, developed and hosted by the KCTU with double data checking for 100% of primary outcome, the first two cases by each individual conducting data entry, and for a random 10% of cases. The trial database has monitoring functions and a full audit trail. Appropriate quality control will be carried out during the trial and before the database lock.

Data protection will be specified and followed, in keeping with Good Clinical Practice and the General Data Protection Regulation 2018. All personal data and audio and video recordings will be held on password protected University of Manchester and NHS secure servers. Copies may also be held in a locked cabinet, on encrypted hard-drives in accordance with pre-specified highly secure procedures. All data will be kept confidential, accessed only by the trial team.

Data will be stored in the Faculty of Biology, Medicine and Health, University of Manchester. Paper copies will be stored centrally in secured cabinets. Electronic data will be stored within the Kings College Clinical Trials Unit secure data storage facility and on University of Manchester supported research storage systems. At the end of the trial, the data will be stored for a period of 15 years before being destroyed. The data custodian will be [name], Chief Investigator of the study.

### Confidentiality {27}

Confidentiality procedures will be pre-specified and followed, in keeping with Good Clinical Practice and the General Data Protection Regulation 2018. Personal information will be collected by researchers during research data collection. Personal information may be shared outside of the research team only with participant consent, e.g. with clinicians involved with the family. The only time that personal information will be shared without consent is if there are serious concerns about the safety or wellbeing of a child or vulnerable adult. In this event, local procedures for safeguarding children and vulnerable adults will be followed. Data collection forms will be identifiable only by participant ID and will contain no names or contact details. Personal and sensitive data will be stored separately and securely on a password-protected section of the university/NHS servers and/or hard drive in secure offices located at University of Manchester and NHS facilities. If personal information needs to be emailed, this will be in an encrypted form.

### Plans for collection, laboratory evaluation, and storage of biological specimens for genetic or molecular analysis in this trial/future use {33}

Not applicable; no biological specimens will be collected.

## Statistical methods

### Statistical methods for primary and secondary outcomes {20a}

A detailed statistical analysis plan will be approved by the Data Monitoring and Ethics Committee (DMEC) and Trial Steering Committee before analysis of unblinded data. Analysis will follow intention-to-treat principles and follow the CONSORT statement for non-pharmacological interventions. Analyses will post-date final follow-up assessments, with due consideration of potential biases from loss to follow-up. Baseline data will be presented using appropriate summary statistics with no testing for baseline differences.

To satisfy Objective 1, treatment effects on the primary and secondary clinical outcomes will be estimated using linear mixed models fitted to outcome variables at all time points. Fixed effects will be centre, baseline assessment for the outcome under investigation, treatment, time, and time×treatment interactions. Participant and group number will be included as random intercepts, treating the control participants as ‘groups’ of size 1. Marginal treatment effects will be estimated for outcomes at each timepoint, and reported separately as mean adjusted differences in scores between the randomised groups with 95% confidence intervals and two-sided *p*-values. The random effect structure will account for repeated measures and clustering due to the partial nested design and allow estimates of the ICC in the intervention arm.

For secondary outcomes only measured at baseline and 52 weeks, the same approach will be used without the time×treatment interaction and time as fixed effects, since there is only one measurement occasion.

For all analyses, each intervention group will contain only the outcome measures on an index caregiver, and so beyond the group-level clustering, no further adjustment for multiple caregivers is required.

#### Health economic analysis

The economic analysis will use a within-trial, intent to treat approach and include all participants randomised to the two trial arms. The primary analysis will use the NHS and social care (costs) and parents/primary caregivers (health benefits) perspectives, with a 12-month time horizon. Costs will be estimated from health and social care service use data collected via the SUI and Caregiver Group-based Interventions Questionnaire. National unit costs will be used to cost each of the services used [61, 62]. Health benefit for the primary analysis is the QALY (EQ-5D-5L version, and published utility tariffs recommended by NICE at the time of the analysis). Health economic regression analysis, adjusted for key covariates, will estimate the net costs and QALYs of the intervention. Missing data will be accounted for in the analyses of net costs, net QALYs, and cost effectiveness acceptability. The methods used to deal with missing follow-up data will be determined according to the extent and pattern of missing data [63–65]. The estimates of net costs and QALYs from the regression analyses will be bootstrapped [66] to simulate 10,000 pairs of incremental cost and QALY outcomes of the intervention. This will include (i) plotting the distribution of pairs of net costs and QALYs on a cost-effectiveness plane, (ii) generating a cost-effectiveness acceptability curve, (iii) estimating the probability that intervention is cost-effective, and (iv) estimating a net benefit statistic. Sensitivity analyses will explore the intervention’s cost-effectiveness using (i) GHQ-30 (caregiver mental health), (ii) the adapted Child Health Utility-9D Index (child wellbeing), and (iii) wider perspective to include indirect costs of lost productivity. A simple decision model will explore the potential cost-effectiveness of the intervention over longer time horizons.

A detailed economics analysis plan will be approved by the DMEC and TSC prior to analysis. The economic evaluation will be reported in line with the Consolidated Health Economic Evaluation Reporting Standards (CHEERS) statement [67].

### Interim analyses {21b}

There will be no planned interim analysis for efficacy or futility.

### Methods for additional analyses (e.g. subgroup analyses) {20b}

No subgroup analyses are planned.

### Methods in analysis to handle protocol non-adherence and any statistical methods to handle missing data {20c}

The primary analysis will be on the intention-to-treat population using a linear mixed model. This approach will allow for missing outcome data under the Missing At Random assumption; we may also use inverse probability weighting to adjust for non-adherence to allocated treatment and other intermediate outcomes as predictors of future loss to follow-up.

### Plans to give access to the full protocol, participant-level data, and statistical code {31c}

The datasets generated and analysed and the corresponding statistical code will be available in anonymised form from the research team on reasonable request, subject to review, following the publication of trial results.

## Oversight and monitoring

### Composition of the coordinating centre and trial steering committee {5d}

The project management group is responsible for the day-to-day conduct of the trial and will meet regularly, at least quarterly, across the course of the trial. The group will be chaired by the Chief Investigator and will comprise trial principal investigators, statisticians and health economists, trial manager, and members of the research and NHS intervention teams, and other invited members as necessary.

The Trial Steering Committee (TSC) will be formed, including an independent chair, parent representatives, an NHS clinician, and an experienced triallist (TSC members listed in the Acknowledgments). The TSC will be consulted on the design, protocol, techniques for ascertainment, and measurement. The TSC will meet at least once prior to the commencement of the trial and at least annually thereafter.

### Composition of the data monitoring committee, its role and reporting structure {21a}

There will be an independent data monitoring and ethics committee (DMEC) comprising three external members who bring methodological, statistical, clinical, and subject-specific expertise and declare no conflicts of interest (DMEC members listed in the Acknowledgements). Its role will be to safeguard the interests of trial participants, assess the safety of the interventions during the trial, and monitor overall trial conduct. The DMEC is independent of the sponsor and funder and will report to the Trial Steering Committee. The DMEC Charter is available on request from [name], King’s College London.

### Adverse event reporting and harms {22}

For all participants, we will collect information about adverse events at each follow-up visit and record adverse events in a standard format. We will capture adverse events that pertain to the trial index adult and the index child. In addition to recording medical adverse events in the standard way, we will also include events particularly relevant to this psycho-social intervention/trial, such as those relating to wellbeing, mental health, and difficult family circumstances.

Information about the adverse event will be collected, including but not exclusive to categorisation, description of event, length of time, start/stop date, ongoing status, relationship to intervention, and whether it is deemed a serious adverse event. It is possible that during the intervention sessions, participants may report “adverse events” to the Trial Practitioners. These will be recorded as part of the therapy log that practitioners will complete after each session. These events will be referred to as ‘therapy reported negative events’ as they will only be applicable to one arm of the Trial. These events will be monitored internally as there is the risk of unblinding researchers. Any serious events will however be reported the same as adverse events.

Adverse events will be monitored by the DMEC and TSC. Serious adverse events will be reported to the project management group and sponsor. If any of the serious adverse events are a suspected unexpected reaction to the intervention (it is acknowledged that this is highly unlikely in this trial), these will be reported immediately to the sponsor, research ethics committee and DMEC.

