##### Experimental intervention

Participants randomised to the experimental treatment arm will access the Empower-Autism programme instead of their usual local post-diagnostic group-based programme offer (where one is offered). Like the TAU group, they will continue to access any general TAU services and interventions on offer in their locality, as per usual care. The Empower-Autism programme is a closed-group manualised and holistic programme, designed to address the needs of a wide range of caregivers in the post-diagnostic period, with a particular focus on caregiver mental health and wellbeing. It is composed of five 3-h sessions, delivered online via video-conferencing. Each programme is delivered by a lead and supporting practitioner and attended by a maximum of 12 participants (with one additional non-trial adult per family, if desired). The programme integrates:*Autism psycho-education*: The programme consists of high-quality, up-to-date, and evidence-informed autism psycho-educational content, including: information about autism, the diversity and complexity of autism presentations including reflection on how it presents within their own child; core characteristics of autism including communication, social interaction, thinking styles, sensory needs, emotion and energy regulation, and behaviour; and child-centred strategies to support each of these areas. First-hand autistic perspectives are included through videos, descriptions, quotes, and exercises and through signposting to materials that offer personal accounts. The aim of the psycho-educational content is caregiver understanding, insight, empathy, and empowerment through knowledge of the condition, practical strategies for use in daily life, and ability to make informed and positive choices for ongoing care. A range of delivery methods are employed to ensure sessions are enjoyable and interactive; to share information, ideas, and experiences; and to consolidate, apply, and extend learning.*Autism context*: This content comprises information about the education system as it relates to children and young people with special educational needs and disabilities, reflection on working together with educational settings, and sources of local, national, and online sources of information and support.*ACT content and philosophy*: Empower-Autism offers an experiential and skills-based introduction to ACT tools, philosophy, and processes to support participants with their own emotional responses to the diagnosis and parenting their child, and to adapt and flex to any challenges that may arise as a result of their child’s condition, the surrounding context, or any other factors. Emphasis is placed on the need for caregivers to value and give time and space for their own emotional wellbeing and stress management. The programme adopts the ACT Matrix [44] as the main delivery framework and includes the following concepts: mindful awareness and pausing; mindful noticing of thoughts, feelings, and physical sensations; cognitive defusion (choosing whether or not to engage with unhelpful thoughts and unhooking from them); expansion (accepting and making space for difficult thoughts and feelings rather than fighting against them); values clarification (reflecting on what is important to you as a person and as a caregiver); and committed action (making a commitment to small steps in a direction consistent with your values). These principles are introduced and reinforced through group discussion, experiential exercises, metaphors, videos, and individual reflection and tasks and are modelled by group facilitators within all discussions and activities. The ACT philosophy asserts the shared humanity and expertise of participants and group facilitators, autism- and neurodiversity-positivity, flexibility and responsiveness to individual needs and group dynamics, and acceptance of and compassion for the diverse range of thoughts, feelings, and experiences brought by group members.*Social support and validation* is promoted through group formation, networking, sharing of experiences and expertise, facilitated group discussions, and linkage to local, national, and online sources of community. Optional ongoing informal peer support is encouraged, for example, through a closed messaging or social media group.*Extension resources:* Extended learning related to the psycho-education and ACT components is offered through physical resources (handouts and information sheets) and online resources through a secure web portal developed by the team during the pre-trial phase and hosted on the University of Manchester server. This includes signposting to existing highly regarded local and national websites, organisations, and sources of information. Home practice suggestions are made at the end of each session and consist of exercises, strategies, or reflections that can be carried out as part of daily life.

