## Data collection and management

### Plans for assessment and collection of outcomes {18a}

Recruitment of participants will be via our partner NHS/local authority diagnostic teams. A member of the local clinical team will initially identify potential participants and screen for eligibility. An NHS practitioner/clinician will then provide a brief introduction of the trial and, with consent, pass over the contact details to the University research team.

All research activity and data collection will be carried out by trained, blinded Research Associates/Assistants in accordance with pre-specified trial standard operating procedures. Due to the COVID-19 pandemic, research activities will take place remotely. Following a referral, an introductory email and the Participant Information Sheet will be emailed to the potential participant. A member of the research team will then contact the family and have a more detailed discussion about the trial, go through the Participant Information Sheet with the participant and answer any questions they may have. Once participants have had sufficient time to consider participating, ask questions, and discuss it with family and friends, the researcher will proceed with fully informed audio-recorded verbal consent. Each case will be registered and assigned a participant ID number. The baseline assessment will then be undertaken by Research Assistants prior to randomisation. Follow-up data collection will take place at 12, 26, and 52 weeks after randomisation.

Data collection will take place remotely wherever possible. Questionnaire data will be collected via post or electronically via email, online survey or via telephone and/or videoconferencing, with visits to participants’ homes only when necessary and COVID-related guidelines permit. Researchers will sit and/or discuss over the phone/videoconference with participants during questionnaire completion to assist with understanding where necessary and to minimise missing data. Interviews will also be completed remotely via telephone and/or videoconferencing, or at the participant home. The Autism Five Minute Speech Sample will be audio-recorded, transcribed, and coded by research staff. Teacher questionnaires will be collected at baseline and endpoint either via school/nursery visits and/or remotely. Data collection forms are available through their publishers/authors; trial-specific forms are available on request.

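### Serious events from therapy logs join the common adverse-event stream with no stated source label, and the reason for keeping non-serious ones internal does not apply to the DMEC

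*Protocol article*

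**What the plan says.** The section on adverse event reporting and harms {22} describes two ways in which an event can come to light.

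- **Both arms, at visits.** "For all participants, we will collect information about adverse events at each follow-up visit and record adverse events in a standard format". The section on assessment and collection of outcomes {18a} gives the times: "Follow-up data collection will take place at 12, 26, and 52 weeks after randomisation".
- **Intervention arm only, at sessions.** Participants may mention events to practitioners during the programme. "These will be recorded as part of the therapy log that practitioners will complete after each session". The description of the experimental intervention gives the number of contacts: "It is composed of five 3-h sessions, delivered online via video-conferencing".

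The protocol sees that the second route is one-sided: "These events will be referred to as ‘therapy reported negative events’ as they will only be applicable to one arm of the Trial". It then sets two rules. For log events in general: "These events will be monitored internally as there is the risk of unblinding researchers". For the serious ones: "Any serious events will however be reported the same as adverse events".

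The same section has adverse events monitored by the DMEC and the Trial Steering Committee. The section on the data monitoring committee {21a} describes the DMEC as three external members, independent of sponsor and funder, whose role is among other things to "assess the safety of the interventions during the trial".

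**The concern.** Two things do not fit together.

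First, the protocol separates log events because only one arm can produce them, then lifts the separation for the serious ones and does not say how their origin will be kept visible. A count of serious events by arm drawn from that stream would compare visits plus sessions with visits alone. Serious events are usually few, so even one or two log-only cases could colour the safety message.

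Second, the reason for keeping the remaining log events internal is that researchers might be unblinded. That is a good reason to keep them from outcome assessors. It is not a reason to keep them from an external committee that collects no data and has intervention safety in its remit. Distress voiced in a session is a direct harm signal for a programme that works on caregivers' emotional responses. The section on discontinuing allocated interventions {11b} itself treats multiple adverse events related to the intervention as relevant to safety, without requiring any one of them to be serious.

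**Working it through.** The protocol states no figure on this point, so there is none to reproduce. The first part is illustrated by arithmetic on assumed inputs. The second is a comparison of the text.

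**Part 1: the extra detection route**

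Inputs:
- Routes by arm: visits in both arms, session logs in the intervention arm only (sections {22} and {18a}, and the intervention description).
- *s*, the probability that a serious event is captured at a visit: not given. Assumed 0.75 to 0.90, equal in both arms. The nearest figure is the 25% attrition in the revised sample size calculations, which is only a loose guide to missed events.
- *t*, the probability that a serious event is captured through a log: not given. Assumed 0.05 to 0.30, independent of visit capture.
- True risk: assumed equal in the two arms.

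Recorded ratio, intervention to treatment-as-usual:

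ratio = [1 − (1 − s)(1 − t)] / s = 1 + t(1 − s)/s

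| s | t | Intervention capture | Ratio |
|---|---|---|---|
| 0.90 | 0.05 | 1 − 0.10 × 0.95 = 0.905 | 0.905/0.90 = 1.006 |
| 0.90 | 0.30 | 1 − 0.10 × 0.70 = 0.930 | 0.930/0.90 = 1.033 |
| 0.75 | 0.05 | 1 − 0.25 × 0.95 = 0.7625 | 0.7625/0.75 = 1.017 |
| 0.75 | 0.30 | 1 − 0.25 × 0.70 = 0.825 | 0.825/0.75 = 1.100 |

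Outside that range, s = 0.60 gives 1.033 at t = 0.05 and 1.20 at t = 0.30. With s = 1 the ratio is 1.00 whatever t is. Under these assumptions the ratio is never below 1, and it exceeds 1 whenever visits miss some events and logs catch some of those.

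In events: the expected number of log-only serious events is N × p × (1 − s) × t. Take N = 256, the intervention-arm figure in the revised sample size calculations, and an assumed true risk p of 5%. At the upper corner this is 256 × 0.05 × 0.25 × 0.30 = 0.96. At the lower corner it is 256 × 0.05 × 0.10 × 0.05 = 0.06. With p of 2% or 10%, the upper corner becomes 0.38 or 1.92.

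After the fix, both arms are counted at visits only, so the ratio is s/s = 1.00 under equal true risk and equal visit capture. Sample size and power are not affected.

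**Part 2: the reason for internal monitoring**

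- Section {22} names researchers as the people at risk of unblinding.
- The section on who will be blinded {17a} lists data collection staff, their supervisors and the senior statistician. It does not list the DMEC.
- Section {21a} makes the DMEC external and gives it intervention safety.
- Section {22} sends adverse events to the DMEC and the steering committee but has therapy-reported negative events monitored internally. On the natural reading of that contrast, the DMEC learns of a non-serious log event only if the participant also reports it at a visit.

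A closed listing to the DMEC would therefore unblind none of the people whom the protocol says it must protect.

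**The case against.** The strongest reply is that the rule on serious events concerns reporting, not analysis. Read where it stands, it sends them along the safety route to the project management group and sponsor and, for suspected unexpected reactions, to the ethics committee and DMEC. That is proper and should not change. A reader might infer that the two sources will be pooled in the final harms table. The document does not say so: it describes no between-arm analysis of serious events, and the analysis plan, which is not shown, may separate them. The log also exists as a separate record, so source can be recovered. All of this stands. The point is therefore limited to any count taken from the common stream, and to the missing statement that source is kept.

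A reader might also infer that the DMEC sees no distress arising in sessions. That goes too far. Visits ask both arms about wellbeing, mental health and family circumstances and record relationship to the intervention, and the DMEC monitors those events. What internal monitoring means is not defined, and the DMEC Charter, which may settle it, is not shown. What remains is that the stated reason does not support leaving the DMEC out.

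Finally, a larger bias can be produced. If visits capture 70% and logs catch half of the rest, capture is 0.70 + 0.5 × 0.30 = 0.85 and the ratio is 0.85/0.70 = 1.21. Nothing in the document supports these inputs. An event after the last session cannot enter a session log, so five sessions catching half of all missed serious events over 52 weeks is implausible. It is also fair to say that any bias overstates harm, which is the cautious direction.

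**Conclusion.** The point holds in limited form and is minor. As written, serious events from a one-arm source enter the same reporting stream as visit events with no stated source label, so a between-arm count from that stream would lean toward more recorded harm in the intervention arm. The lean is probably small: a ratio of about 1.01 to 1.10, given equal true risk, equal visit capture of 75% to 90% and log capture of 5% to 30%. None of these inputs is in the document, so the size cannot be fixed from it. Separately, the risk of unblinding researchers does not justify keeping therapy-reported negative events from an independent DMEC. That they are kept from it is the natural reading of the text, not an explicit statement. The primary outcome, power and efficacy analysis are untouched.

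**What to change.** 1. Keep the safety reporting of serious events exactly as it is.
2. Tag each event by source: visit, therapy log, or both. Hold the tag where blinded researchers cannot see it, because a log entry reveals the arm. Recruitment ended on 19/04/22, but logs are completed after each session, so the tag can be assigned from existing records.
3. Base the between-arm comparison of serious events on those ascertained at the follow-up visits common to both arms, whether or not they also appear in a log. Tabulate log-only serious events separately for the intervention arm.
4. Give the DMEC the therapy-reported negative events as a one-arm listing in its closed report. The Trial Manager already receives allocations, so the listing can be compiled without unblinding anyone further.

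The cost is a source tag, one extra table and one extra DMEC listing. The visit-only comparison still assumes similar visit capture in the two arms, so visit attendance by arm should be shown beside it.
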